## Abstract

**Purpose:**

Migraine, a leading global cause of disability, affects over 1.1 billion individuals worldwide. Current acute pharmacotherapy is limited by contraindications and adverse events (AEs), underscoring the need for safer, more effective alternatives. The Sishun Formula (SSF), a traditional Chinese medicine (TCM) formulation targeting “Ying-Wei disharmony,” demonstrated promising preclinical and preliminary clinical results. This trial aims to rigorously evaluate SSF’s efficacy and safety for acute migraine attacks.

**Patients and methods:**

This multicenter, randomized, double-blind, placebo-controlled trial will enroll 144 participants with acute migraine and “Ying-Wei disharmony” syndrome, randomized 1:1 to SSF or placebo. A single dose of SSF or a matched placebo is administered within 0.5 h of migraine onset. The primary outcome is the proportion achieving headache freedom at 2 h post-dose. Secondary outcomes include the proportion achieving headache relief at 2 h post-dose, absence of most bothersome associated symptoms, sustained relief/freedom at 24/48 h, the Visual Analogue Scale (VAS) score changes, time to efficacy onset, recurrence rates, and TCM syndrome improvement. Biomarkers [e.g., calcitonin gene-related peptide (CGRP)] and safety parameters (vital signs, laboratory tests, AEs) are monitored. Data analysis will employ SPSS 25.0 and R 4.3.1.

**Conclusion:**

The findings are anticipated to deliver high-quality evidence validating SSF’s efficacy and safety, offering a promising therapeutic alternative for acute migraine attacks.

**Clinical trial registration:**

http://itmctr.ccebtcm.org.cn/, identifier ITMCTR2025000187.

## Introduction

1

Migraine ranks as the 3rd leading cause of disability-adjusted life-years (DALYs) among all nervous system disorders globally, and the top cause of DALYs in adolescents (5–19 years). It affects 14.9% of the global population (1.16 billion individuals), making it the most prevalent neurological condition by prevalence (1). Beyond its hallmark pain, the acute migraine attack is often associated with photophobia, phonophobia, nausea, and vomiting. These symptoms exacerbate disability, disrupt daily activities, and elevate risks of comorbid conditions such as anxiety, depression, and cardiovascular disorders (2). Guidelines indicate that acetaminophen, acetylsalicylic acid, ibuprofen, naproxen sodium, and triptans have the highest level of evidence for the treatment of acute migraine attacks (3, 4). In recent years, gepants have emerged as novel calcitonin gene-related peptide (CGRP) receptor antagonists offering a favorable safety profile for acute migraine treatment, particularly in patients with contraindications (5). Despite the availability of these medications, many patients experience inadequate relief from their symptoms (6). It was reported that a significant proportion of migraine sufferers (60–88%) failed to achieve pain freedom at 2 h after taking the triptans (7). Additionally, frequent use of these medications may lead to adverse events (AEs) such as medication-overuse headaches, gastrointestinal complications, and cardiovascular events (6, 8, 9), underscoring the urgent need for safer, more effective alternatives.

Traditional Chinese medicine (TCM) attributes migraine pathogenesis to imbalances in Ying and Wei, collectively termed “Ying-Wei disharmony” (10). According to TCM theory, Ying (nutritive Qi) and Wei (defensive Qi) govern physiological harmony, with their disharmony manifesting as disordered Qi-blood circulation and compromised visceral function, ultimately triggering migraine (11). In modern medicine, Ying and Wei are recognized as essential substances responsible for maintaining homeostasis of the vascular intima and adventitia, as well as balancing energy metabolism and immune defense (12). Ying-Wei imbalance is associated with key pathological mechanisms of migraine, including dysregulation of neuroinflammatory pathways, mitochondrial metabolic dysfunction, autonomic nervous system dysfunction, and impaired vasomotor activity (12).

Based on this theoretical framework and incorporating the extensive clinical expertise of TCM specialist [name], we developed the Sishun Formula (SSF) (13). It is a pharmacologically optimized compound comprising five medicinal botanicals (constituent details provided in Table 1), each with documented analgesic and anti-inflammatory properties as evidenced by modern studies (14–18). Our preclinical studies in migraine-model rats demonstrated that SSF significantly reduced serum and trigeminal ganglion (TG) levels of CGRP while elevating 5-hydroxytryptamine (5-HT) concentrations, with concomitant downregulation of nuclear factor-kappa B (NF-κB) and cyclooxygenase-2 (COX-2) protein expression in TG tissues, thereby ameliorating neurogenic inflammation (19).

**Table 1 tab1:** The Chinese herbal components and dose of SSF.

Chinese name	Botanical nomenclature with taxonomic classification	Dosage (g)	Processed botanical material
Guizhi	*Cinnamomum cassia* (L.) J. Presl (Lauraceae)	10	Dried twig
Baishao	*Paeonia lactiflora* Pall. (Paeoniaceae)	10	Dried root
Chuanxiong	Conioselinum anthriscoides “Chuanxiong” (Apiaceae)	10	Dried root and rhizome
Niuxi	*Achyranthes bidentata* Blume (Amaranthaceae)	10	Dried root
Hongjingtian	Rhodiola crenulata (Hook.f. & Thomson) H.Ohba (Crassulaceae)	6	Dried root and rhizome

However, robust clinical validation through randomized controlled trials (RCTs) remains absent, limiting its integration into evidence-based practice. Therefore, this study will implement a multicenter, randomized, double-blind, placebo-controlled trial to further evaluate the efficacy and safety of SSF for acute migraine attacks. By employing the internationally recognized efficacy endpoints and integrating dynamic monitoring of neuropeptide biomarkers, we aim to elucidate the therapeutic mechanisms of SSF within a modern research framework and provide a safe and effective alternative option for migraineurs.

## Methods and analysis

2

### Formulation preparation

2.1

SSF, classified as a Type A botanical extract under pharmacopoeial standards (20), is a phytopharmaceutical formulation comprising five pharmacologically standardized botanical drugs processed through modern pharmaceutical techniques, including decoction, concentration, drying, and granulation (Supplementary material 1). The formula integrates *Cinnamomum cassia* (L.) J. Presl (Lauraceae; Guizhi-dried twig) (10 g), *Paeonia lactiflora* Pall. (Paeoniaceae; Baishao-dried root) (10 g), *Conioselinum anthriscoides* “Chuanxiong” (Apiaceae; Chuanxiong-dried root and rhizome) (10 g), *Achyranthes bidentata* Blume (Amaranthaceae; Niuxi-dried root) (10 g), and *Rhodiola crenulata* (Hook.f & Thomson) H.Ohba (Crassulaceae; Hongjingtian-dried root and rhizome) (6 g), harmonizing to regulate Ying, Wei, Qi, and Blood, and is therefore named “Sishun.” Quality control protocols employ high-performance liquid chromatography (HPLC) to validate botanical authenticity, quantify bioactive markers, and ensure batch-to-batch consistency, adhering to standard pharmacopoeial specifications for identity, purity, and extraction efficiency (21). Dosage parameters align with evidence-based clinical practices, utilizing processed botanical materials standardized to their pharmacologically active forms for optimized therapeutic delivery. The Chinese herbal components and dose of SSF are presented in Table 1.

### Trial design

2.2

This is a multicenter, randomized, double-blind, placebo-controlled, single-attack clinical trial conducted across three centers: Dongzhimen Hospital affiliated to Beijing University of Chinese Medicine, Xiyuan Hospital of China Academy of Chinese Medical Sciences, and Beijing Tiantan Hospital affiliated to Capital Medical University. A total of 144 eligible participants will be randomized in a 1:1 ratio to either the experimental group (SSF) or the control group (placebo). The study comprises a 4-week screening period, a 45-day intervention period, and a 7-day follow-up period. During the intervention phase, participants will administer SSF or placebo upon experiencing an eligible acute migraine attack, with efficacy and safety assessments conducted at the pre-dose time point after headache onset, 0.5 h, 1.0 h, 2.0 h, 4.0 h, 24 h, and 48 h post-dose. An eligible acute migraine attack must meet two criteria: (1) No prior use of migraine-specific medications (including all Western pharmaceuticals, TCM formulations in any dosage form, or TCM patent medicines explicitly approved for migraine treatment in their prescribing information) within the 24-h period preceding the current episode; (2) The current migraine episode is of moderate to severe intensity [Visual Analogue Scale (VAS) ≥4 scores].

The protocol adheres to the Standard Protocol Items: Recommendations for Interventional Trials (SPIRIT) 2025 guideline (22). The study flowchart is provided in Figure 1, with enrollment, intervention, and assessment timelines detailed in Table 2.

**Figure 1 fig1:**
[figure not shown]
Study flowchart. SSF, Sishun Formula; VAS, Visual Analogue Scale; MAS, migraine-associated symptom; MBAS, most bothersome associated symptom; CGRP, calcitonin gene-related peptide; PACAP, pituitary adenylate cyclase-activating polypeptide.

**Table 2 tab2:** SPIRIT 2025 participant timeline: schedule of enrollment, interventions, and assessments.

Items	Trial period							
	Screening period	Baseline period	Intervention period (waiting for an eligible migraine attack within 45 days)					Follow-up period
Timepoint	−5 to −1 weeks	−1 to 0 weeks	Within 0.5 h of headache onset	Pre-dose time point after headache onset	0.5 h, 1.0 h post-dose	2.0 h, 4.0 h, 24 h post-dose	48 h post-dose	7 days post-dose
Enrollment								
Eligibility screen	X	X						
Informed consent		X						
Randomization		X						
Intervention								
Sishun Formula, once			X					
Placebo, once			X					
Information collection								
Demographic data	X							
Medication history	X	X						
Migraine episode characterization	X	X						X
Efficacy assessment								
VAS score				X	X	X	X	
Migraine-associated symptoms				X		X	X	
Most bothersome associated symptom				X		X	X	
Migraine recurrence						X	X	
Ying-Wei disharmony syndrome score		X					X	X
Acute analgesic utilization				X	X	X	X	
Plasma CGRP, PACAP, and other indicators		X					X	
Safety assessment								
Complete blood count		X					X	
Urinalysis		X					X	
Liver and kidney function test		X					X	
ECG		X					X	
AE					X	X	X	X
SAE					X	X	X	X

h, hour; VAS, Visual Analogue Scale; CGRP, calcitonin gene-related peptide; PACAP, pituitary adenylate cyclase-activating polypeptide; ECG, electrocardiogram; AE, adverse event; SAE, serious adverse event.

“X” indicates required procedures at designated time points.

### Participants

2.3

#### Diagnostic criteria for migraine

2.3.1

According to the diagnostic criteria for “migraine without aura” and “migraine with typical aura” outlined in the International Classification of Headache Disorders, 3rd edition (ICHD-3) (23).

#### Diagnostic criteria for “Ying-Wei disharmony” syndrome

2.3.2

This syndrome is characterized by the presence of at least one of the following clinical features: (1) aversion to wind; (2) spontaneous sweating; (3) cold intolerance or cold extremities; (4) mental fatigue; and (5) palpitations. The differentiation of the syndrome will be independently assessed by two qualified researchers.

#### Inclusion criteria

2.3.3

Eligible participants must fulfill all the criteria listed below:

Patients who both meet the diagnostic criteria for migraine and “Ying-Wei disharmony” syndrome.Patients who are aged 18–65 years (inclusive).Patients whose first migraine episode occurred before the age of 50.Patients who have a documented migraine history of at least 1 year.Patients who experience 2 to 8 moderate-to-severe migraine attacks (VAS ≥4 scores) within the past 4 weeks, with a minimum interval of 48 h between consecutive episodes.Patients must be able to distinguish migraine from other types of headaches, such as tension-type headaches.Patients who voluntarily participate in the study with written informed consent provided by the participant or their legal guardian.

#### Exclusion criteria

2.3.4

Participants meeting any of the following criteria will be excluded:

Patients with ≥15 migraine days within the past 4 weeks.Patients who have used analgesics for ≥10 days within the past 4 weeks.Patients with secondary headaches attributed to organic pathologies, including but not limited to subarachnoid hemorrhage, cerebral hemorrhage, cerebral infarction, vascular malformations, arteritis, hypertension, or atherosclerosis.Patients with severe circulatory, digestive, respiratory, or hematopoietic system diseases or cancer.Patients with a history of epilepsy, stroke, other neurological disorders, or psychiatric conditions.Patients with severe liver diseases, or those presenting with abnormal liver function, defined as aspartate aminotransferase (AST) or alanine aminotransferase (ALT) levels greater than 1.5 times the upper limit of the normal range (ULN).Patients with severe kidney diseases, or those presenting with abnormal kidney function, defined as creatinine (Cr) levels exceeding the ULN.Patients exhibiting significant anxiety or depression symptoms [Hamilton Anxiety Rating Scale (HAMA) ≥15 scores or Hamilton Depression Rating Scale (HAMD) ≥18 scores].Patients with cognitive impairment, manifested as an inability to read or comprehend assessment scales, non-compliance with medical treatment, or inability to complete efficacy evaluations.Patients using migraine prophylaxis at stable doses for <3 months.Patients who are pregnant, lactating, or planning pregnancy.Patients currently participating in other clinical trials.

#### Withdrawal/termination criteria

2.3.5

Participants will be discontinued from the study if any of the following criteria are met:

Patients who voluntarily request to discontinue their participation in the study.Patients who are unable to follow the study procedures or become lost to follow-up during the trial period.Patients who experience serious AEs.Patients with pregnancy detected after trial enrollment.Patients demonstrating absence of an eligible acute migraine attack within 45 days after enrollment.

### Randomization and allocation

2.4

The randomization scheme was designed and managed by an independent statistical unit using block randomization methodology. A random allocation sequence was generated through the PROC PLAN procedure in the Statistical Analysis System (SAS) V9.4 software. The randomization procedure was supervised by statisticians from the Good Clinical Practice (GCP) Center at Dongzhimen Hospital, Beijing University of Chinese Medicine. Critical parameters, including the selected block size and randomization table, were sealed and stored at the GCP center of Dongzhimen Hospital. Study medication allocation across trial sites commenced with the lowest assigned identifier, with eligible participants receiving drugs sequentially according to enrollment chronology.

### Blinding

2.5

Blinding was administered by an independent statistical unit without direct involvement in trial operations. The team reviewed the trial medications and placebos to ensure their consistency in appearance and odor. Subsequently, the team standardized the drugs’ packaging and labeling configurations, with preassigned randomization codes affixed to all pharmaceutical containers. The blinding protocols were thoroughly documented and archived under restricted access. Emergency unblinding is permitted when investigators deem immediate intervention imperative for participant safety. However, the reasons for unblinding, the date of the procedure, and the signature of the site principal investigator must be fully documented.

### Intervention

2.6

A single dose of granule therapy is to be administered to both groups within 0.5 h following the onset of an eligible migraine attack. Patients in the treatment group are orally administered SSF granules (2 bags at 7.78 g each, with warm water) within 0.5 h of headache onset. Patients in the control group are orally administered placebo granules (2 bags at 7.78 g each, with warm water) within 0.5 h of headache onset. Both SSF and placebo granules were produced by Sichuan Neo-Green Pharmaceutical Technology Development Company Limited. The placebo was formulated with maltodextrin, coloring agents, bittering agents, and 5% of the SSF herbs to sensorily match the active granules in appearance, taste, and odor, thereby protecting blinding integrity while ensuring negligible pharmacological activity.

Additionally, researchers will provide migraine management counseling to both groups. During the clinical trial period, patients may utilize alternative acute analgesic treatments for headache episodes that do not meet eligibility criteria, provided they contact researchers for treatment registration. In cases where the trial drugs fail to alleviate symptoms during an eligible migraine attack (i.e., no improvement in headache severity, impairments in daily or occupational functioning, or mood alterations), researchers will maintain open communication with patients, permit the use of conventional Western acute analgesics under supervision, and provide guidance on medication administration and post-intervention monitoring. Participants will also be instructed to record the timing and type of rescue medication used.

### Outcomes and measurements

2.7

Efficacy evaluation is conducted through a specifically designed migraine patient-reported form. Patients are instructed to document migraine severity and migraine-associated symptoms (MASs) at pre-dose and at 0.5, 1, 2, 4, 24, and 48 h post-dose (24). To ensure data accuracy, physicians will review all entries in the form. In cases of implausible or inconsistent data, the attending physician will further inquire with the patient to verify the reported information. Pain intensity is quantified using the VAS and categorized into four severity levels: 0 (no pain), 1–3 (mild pain), 4–6 (moderate pain), and 7–10 (severe pain). To ensure reliable self-assessment during migraine attacks, all participants receive structured pre-trial training on the use of the VAS. This training includes standardized verbal instructions and practical examples to enhance comprehension and consistency in real-time reporting. Additionally, a simplified VAS guide emphasizing anchor points (e.g., “0 = no pain,” “10 = worst imaginable pain”) is provided for quick reference. The MASs, including photophobia, phonophobia, nausea, and vomiting, are assessed via a binary scale (0 for absence; 1 for presence) (25). Detailed outcome measurements at each time point are summarized in Table 2.

#### Primary outcome

2.7.1

The primary endpoint is the proportion of patients achieving headache freedom at 2 h post-dose. Headache freedom is defined as the reduction in headache severity from baseline moderate or severe to no pain, as measured by the VAS.

#### Secondary outcomes

2.7.2

The proportion of patients achieving absence of the most bothersome associated symptom (MBAS) at 2 h post-dose. Patients will self-identify their MBAS from the following symptoms at migraine onset: photophobia, phonophobia, nausea, or vomiting.The proportion of patients achieving headache relief at 2 h post-dose. Headache relief is defined as the reduction of initial pain intensity from moderate to severe levels down to mild or no intensity.The proportion of patients sustaining headache relief from 2 to 24/48 h post-dose. Sustained headache relief from 2 to 24/48 h is defined as achieving headache relief without rescue medication use and the absence of moderate-to-severe headache recurrence during 2 to 24/48 h following initial treatment.The proportion of patients sustaining headache freedom from 2 to 24/48 h post-dose. Sustained headache freedom from 2 to 24/48 h is defined as achieving headache freedom without rescue medication use, coupled with the absence of any headache recurrence (mild, moderate, or severe) during 2 to 24/48 h following initial treatment.Change in VAS scores from pre-dose to 0.5, 1, 2, 4, 24, and 48 h post-dose.Time to onset of efficacy, defined as the interval (in minutes) between drug administration and headache relief.Headache recurrence rate between 2 and 48 h post-dose. Headache recurrence is defined as patients who achieved headache relief (freedom) at 2 h post-dose, reexperiencing moderate-to-severe headache (headache of any severity) within the 2 to 48 h post-dose window.Change in TCM “Ying-Wei disharmony syndrome.” The syndrome will be assessed using the Ying-Wei Disharmony Assessment Scale (YWDAS) at baseline, 48 h post-dose, and 7 days post-dose. The scale comprises five core TCM syndromes, and the assessment framework is detailed in Table 3. Its development was grounded in clinical expertise from senior TCM practitioners and integrated classical and contemporary medical literature. Content validity was established through a rigorous review and consensus by a panel of five senior TCM experts. In a pilot study to assess feasibility and inter-rater reliability, all YWDAS assessments were independently performed by two TCM researchers who underwent standardized training using predefined scoring criteria to minimize assessment bias. The inter-rater reliability, assessed by the intraclass correlation coefficient (ICC) for absolute agreement, was 0.76 (95% CI: 0.64–0.84), indicating good agreement.

**Table 3 tab3:** The Ying-Wei Disharmony Assessment Scale.

Symptom	None (0 point)	Mild (1 point)	Moderate (2 points)	Severe (3 points)	Score
Aversion to wind	Absent	Marked aversion when exposed to the draft	Marked aversion, even without wind exposure	Severe aversion unrelieved by added clothing	
Spontaneous sweating	Absent	Occasional hyperhidrosis or marked post-exercise sweating	Frequent sweating during daily activities	Frequent hyperhidrosis unrelated to physical exertion	
Cold intolerance	Absent	Subjective cold sensitivity	Subjective cold sensitivity and cold extremities	Cold extremities unrelieved by added clothing	
Palpitations	Absent	Exercise/effort-induced, relieved by rest	Frequent occurrence, relieved by rest	Frequent occurrence, unrelieved by rest	
Mental fatigue	Absent	Occasional fatigue, minimal work/study impact	Frequent fatigue with work/study impairment	Debilitating fatigue with significant functional decline	

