### Statistical analysis

2.11

All statistical analyses will be performed using SPSS 25.0 and R 4.3.1 software. Baseline characteristics will be presented through descriptive statistics [mean ± standard deviation or median (interquartile range) or frequency (percentage)]. For between-group balance testing, independent samples *t*-tests will be employed for normally distributed data with homogeneity of variance, while Mann–Whitney *U* tests are used otherwise. Categorical variables will be analyzed using chi-square tests or Fisher’s exact test based on expected frequencies. All predetermined potential confounders will be included as covariates in subsequent models for adjustment, regardless of their between-group balance status. Additionally, baseline variables showing significant imbalance will undergo sensitivity analyses to assess their confounding effects.

Efficacy analyses will be performed on both intention-to-treat (ITT) and per-protocol (PP) populations, with the ITT set including all randomized participants analyzed according to their allocated groups, regardless of protocol deviations, while the PP set will consist of participants who complied with the trial procedures without major deviations. For efficacy assessment, the use of rescue medication before the 2-h time point will be considered a treatment failure for the primary and key secondary endpoints (e.g., headache freedom, headache relief, absence of most bothersome symptom) (26). Accordingly, participants will be included in the 2-h efficacy analysis only if they have not used rescue medication before that time point, even if medication is taken afterward. Similarly, the assessment of sustained outcomes (e.g., sustained headache freedom at 24/48 h) will require no use of rescue medication within the respective 24/48-h timeframe.

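### The 2-h most-bothersome-symptom endpoint does not require the symptom to be present at dosing and allows vomiting on a point-in-time yes/no scale, so some results can carry little treatment information

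*Protocol article*

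**What the plan says.** All references are to the protocol article.

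- **Endpoint (2.7.2).** "The proportion of patients achieving absence of the most bothersome associated symptom (MBAS) at 2 h post-dose". The symptom is chosen by the patient: "Patients will self-identify their MBAS from the following symptoms at migraine onset: photophobia, phonophobia, nausea, or vomiting". Neither sentence sets a condition on the state at dosing or names a denominator.
- **Neighbouring endpoints.** The primary endpoint (2.7.1) does set such a condition: "Headache freedom is defined as the reduction in headache severity from baseline moderate or severe to no pain". Headache relief in 2.7.2 likewise starts from moderate-to-severe pain.
- **Attack eligibility (2.2).** "An eligible acute migraine attack must meet two criteria". One is no migraine medication in the previous 24 h. The other concerns pain only: "The current migraine episode is of moderate to severe intensity [Visual Analogue Scale (VAS) ≥4 scores"]. No associated symptom is needed.
- **Scale (2.7).** The associated symptoms "are assessed via a binary scale (0 for absence; 1 for presence"). They are recorded at each time point, and no look-back interval is stated.
- **Schedule (Table 2).** The most bothersome associated symptom (MBAS) is recorded at the pre-dose time point and again at 2 h.
- **Analysis (2.11).** Efficacy uses the ITT and per-protocol sets, "with the ITT set including all randomized participants analyzed according to their allocated groups". Missing data are multiply imputed. On rescue, "the use of rescue medication before the 2-h time point will be considered a treatment failure for the primary and key secondary endpoints", and absence of the MBAS is listed as an example of these endpoints. It forms a Holm–Bonferroni family of two with headache relief at 2 h.

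**The concern.** A symptom can respond to treatment only if it is there when treatment is given. As written, the endpoint admits two groups for whom this may fail.

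1. **Participants with no associated symptom at dosing.** Section 2.2 lets them treat an attack, and section 2.11 keeps them in the analysis set. Followed literally, the text leads to a rating of 0 at 2 h, which reads as absence, or to a missing value that is then imputed for a symptom they never had.
2. **Participants who choose vomiting.** Someone who vomited before dosing, is still nauseated at 2 h and is not vomiting at that moment counts as a success.

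Such results occur in both arms alike. They raise both rates and narrow the difference. The reported absence rate also becomes harder to compare with other trials, which the Discussion gives as a purpose of the chosen outcomes.

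**Working it through.** **The plan's own figure.** Section 2.9 gives 60 per arm for the primary endpoint: 35% vs 11%, one-sided 0.025, power 90%. With unpooled variance and the difference tested against zero:

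n = (1.960 + 1.282)² × (0.35 × 0.65 + 0.11 × 0.89) / 0.24² = 10.51 × 0.3254 / 0.0576 = 59.4, rounded up to 60.

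The figure reproduces, but it does not concern the MBAS endpoint, for which the article gives no rate and no power.

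**Inputs for the MBAS endpoint**
- 72 per arm (section 2.9).
- Absence rates where the symptom can respond: 45% vs 25%. This is an assumption.
- Share f scored absent in both arms regardless of treatment: 0 to 30%. This is an assumption.
- Two-sided 0.05, and 0.025 for the first Holm step in a family of two.

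**Formulas**
- Observed rate in an arm = f + (1 − f)p.
- Risk difference = (1 − f)(p₁ − p₂), because f cancels between arms.
- Power = Φ{[Δ√n − z√(2p̄(1 − p̄))] / √(p₁(1 − p₁) + p₂(1 − p₂))}, with Δ the risk difference and p̄ the mean of the two rates.
- Restricted analysis: the same formula with 45% vs 25% and n = 72(1 − f).

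**Worked case, f = 20%**
- Rates: 0.20 + 0.80 × 0.45 = 0.56 and 0.20 + 0.80 × 0.25 = 0.40; difference 0.16.
- Diluted: [0.16 × 8.485 − 1.960 × 0.7065] / 0.6974 = −0.039, power 48.4%.
- Restricted, n = 57.6: [0.20 × 7.589 − 1.960 × 0.6745] / 0.6595 = 0.297, power 61.7%.

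| f | Diluted rates | Difference | Power, diluted | Power, restricted | At 0.025: diluted / restricted |
|---|---|---|---|---|---|
| 0 | 45% / 25% | 20 points | 71.5% | 71.5% | 61.1% / 61.1% |
| 5% | 47.75% / 28.75% | 19 | 65.3% | 69.3% | 54.2% / 58.5% |
| 10% | 50.5% / 32.5% | 18 | 59.3% | 66.9% | 48.0% / 55.9% |
| 20% | 56% / 40% | 16 | 48.4% | 61.7% | 37.3% / 50.4% |
| 30% | 61.5% / 47.5% | 14 | 39.1% | 55.9% | 28.8% / 44.5% |

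**Variations**
- *Vomiting choosers absent only 70–100% of the time, equally in both arms.* The difference still shrinks by (1 − f). At f = 10% it is 18 points, with power 59–60%.
- *Symptom-free participants scored as failures instead.* At f = 20% the rates are 36% and 20%, with power 57.2%. This is still below the restricted 61.7%.
- *Other assumed rates, 55% vs 30%, f = 20%.* Power is 67.6% diluted against 78.2% restricted.
- *Odds ratio, since section 2.11 uses logistic regression.* True: (0.45/0.55)/(0.25/0.75) = 2.45. At f = 20%: (0.56/0.44)/(0.40/0.60) = 1.91.

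The factor (1 − f) applies to participants scored absent. If they are imputed instead, the effect on the difference depends on the imputation model, but the imputed values answer a question that does not arise for them. The power figures are for an unadjusted comparison of proportions.

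**The case against.** The case against has several parts, and some of them stand.

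- **Nothing scores a symptom-free participant as absent.** This is correct. A reader might infer that the plan counts such people as automatic responders, but the text is silent: they have no symptom to identify, and the full protocol or SAP may deal with them. What remains is that the article fixes the baseline state for headache freedom and headache relief but not for this endpoint, while its general rules (all randomised, impute what is missing) point toward including these participants.
- **Treatment is not irrelevant to the result.** A reader might infer that these participants succeed whatever the treatment does. That is too strong. Rescue before 2 h is a failure for this endpoint, and vomiting can be recorded as present at 2 h.
- **Onset versus pre-dose is not a real conflict.** Table 2 already schedules the MBAS record pre-dose, and section 2.6 puts dosing within 0.5 h of onset. A symptom that is chosen at onset and gone before dosing needs a narrow sequence of events. This stands; only the wording needs aligning.
- **Vomiting is a legitimate choice.** Nausea is offered separately, physicians review the entries, and no figure in the article shows how often vomiting choosers would be rated absent. The frequency is indeed unknown. Even so, a participant who is still nauseated can count as a success under the stated scale.
- **The size is assumed, and restriction costs power.** At f = 2% the two analyses differ little (69% vs 71%). The fall from 71.5% to 61.7% at f = 20%, however, compares restriction with a trial that has no such participants. Against the diluted analysis of the same trial, restriction is better at every f above zero that was examined.

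**Conclusion.** The point holds as a worthwhile, inexpensive improvement to one multiplicity-controlled secondary endpoint. Its definition does not condition on the symptom being present at dosing, and it admits an episodic symptom on a momentary yes/no rating. Results that carry little treatment information can therefore enter the comparison, and those scored absent shrink the risk difference by roughly (1 − f).

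The size cannot be fixed from the article. Under the assumed 45% vs 25%, the gap in power between the diluted and restricted analyses is about 4 points at f = 5%, 8 at 10% and 13 at 20%.

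The bias is toward the null. A reader might infer a risk of false-positive claims or a threat to the main result, and the documents support neither. The Holm procedure stays valid, and the primary endpoint and sample size are unaffected.

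**What to change.** 1. In section 2.7.2, state that the MBAS is identified at the pre-dose record already scheduled in Table 2, from among the symptoms present then.
2. In sections 2.7.2 and 2.11, analyse this endpoint in dosed participants with an MBAS present pre-dose. Participants with none are outside the denominator and are not imputed. Report their number by arm.
3. Either merge nausea and vomiting into one option, or count a participant who chose vomiting as MBAS-free only if both nausea and vomiting are absent at 2 h. Those who chose vomiting then stay in the analysis with a more informative result. If the options are merged, settle the patient form before data collection.

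The cost is wording in two sections and at most one line on the form. The four symptoms are already recorded pre-dose and at 2 h. Selection rests on data recorded before dosing under blinding, so it does not disturb the randomised comparison. The downside is a slightly smaller denominator: 72 × 0.9 = 64.8 per arm if 10% have no symptom.
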